## 2. Materials and Methods

This multicentric prospective randomized controlled superiority trial will focus on assessing the benefits of our therapeutic protocol on independence in daily life activities, neuropsychological aspects of different spatial components of USN (personal, extra-personal and representational neglect) and egocentric spatial perception assessments, using a mixed measurement design. The HEMISTIM protocol will take place in three neurological rehabilitation centers in Grand-Est and Provence-Alpes Côte d’Azur regions, France.

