#### 2.4.1. Inclusion in Groups

The first week will allow us to include patients with left USN and to randomly assign them to four independent parallel groups (centralized randomization in a 1:1 ratio performed using a custom made algorithm on Matlab (MathWorks, Inc., Natick, MA, USA) by a blinded investigator: a control group receiving no additional treatment to conventional occupational therapy sessions and three experimental groups receiving in addition to the usual treatment either left-NMV, left-NMV + sham-tDCS or left-NMV + a-tDCS experimental treatments, administered by trained occupational therapists.

In these three experimental groups, each patient will be equipped with vibratory stimulators during conventional occupational therapy sessions taking place on Monday, Wednesday and Friday for three weeks from the second week on. The left-side NMV vibrator will be activated during the first 15 min of the occupational therapy session (lasting 45 min), as previously described [21,35]. In the two experimental groups receiving sham or a-tDCS, electrodes will be placed as described above. A continuous 2 mA current will be delivered for 20 min in the left-NMV + a-tDCS group, 5 min before (patients will be seated in a quiet room) and during the first 15 min of the occupational therapy session, simultaneously to the NMV stimulation. The current will be automatically turned off after 20 s in the left-NMV + sham-tDCS group, allowing the reproduction of the initial mild itching sensation at the beginning of active tDCS, thus ensuring that the patient stays blind to the activation status of the device. In the case of adverse events or unintended effects of trial interventions, the investigator who enrolled the patient will report its occurrence to the trial sponsor through a report form provided in the case report form.

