### 2.5. Sample Size Calculation

To determine the number of left USN patients to include, we sought to perform an a priori headcount calculation based on published work in the field. However, none of them have combined NMV and tDCS or used the CBS score as the primary endpoint. No a priori power calculation could therefore be performed, but we were inspired by the number of patients included in the works of Làdavas et al. [32] and Turgut et al. [33], both of whom used tDCS on USN patients, the former combined with visual prisms and the latter with optokinetic drift. These two studies included 30 and 32 patients, respectively, which were divided for the first in two groups of 11 patients and one group of 8, and for the second in two groups of 16 patients. Thus, we estimated that 48 patients would be necessary for our study, randomly and homogeneously distributed in each of the 4 groups. To ensure that the target number of patients is recruited, three neurological rehabilitation centers admitting each year a large number of patients meeting the inclusion criteria will be involved. We will verify a posteriori that the groups do not differ in sex, mean age, education, duration of illness, or baseline CBS scores, and that they have similar stroke locations.

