### 2.6. Statistical Analysis

CBS scores, those of personal neglect, mean egocentric errors and mental evocation, the time needed to finish the wheelchair course and the number of bumps in each direction will be entered as quantitative data.

After having verified the required assumptions about data distributions (Shapiro–Wilk test of normality, Levene’s test of homoscedasticity, Box’s M-test of covariance homogeneity and Mauchly’s test of sphericity), a mixed analysis of variance (with repeated measures for the SSA) will be performed on each quantitative variable with test periods (Pre, Postsession1, Postweek1, Postweek3, Postweek6) as within-subject factors and treatment groups (control, left-NMV, left-NMV + sham-tDCS, left-NMV + a-tDCS) as between-subject factors. Post hoc tests will be conducted using Tukey’s honestly significant difference method when needed, and *p*-values will be adjusted with the Bonferroni method. Size effects will be reported using the η2 (Eta-square) for each ANOVA and Cohen’s d for each Tukey’s post hoc test, along with confidence intervals.

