
There are some inherent features of our study protocol that deserve cautious consideration. Particular attention will be directed to the phenomena of limb activation and motor extinction [36,37], since our protocol is designed around the performance of voluntary upper limb movements simultaneously to stimulation sessions in USN patients. Although it has been shown in the literature that the use of the contralesional arm in the neglected hemi-space significantly reduces the severity of USN [37], these patients generally have great difficulty in mobilizing it in the early post-stroke stages. Moreover, the simultaneous use of both upper limbs in the neglected hemi-space limits or even suppresses the previously observed beneficial effects [36,37] possibly by perceptual “overshadowing” of the contralesional arm movements by the ipsilesional ones, according to Robertson and North [37]. Therefore, the therapists will carefully avoid bimanual activities in the neglected hemi-space, but exercises will be allowed with the right upper limb instead of the left one if the latter is too impaired to effectively perform them in initial phases of rehabilitation. This gradual increase in task complexity is also intended to maintain high motivation levels. Other vigilance points will be taken into account. We will be watchful of population homogeneity, hence the need to include a sufficient number of patients. We will compare the evolution of each patient from baseline according to his affiliation group, given the possibility of inter-subject variability in responsiveness. In addition, the long-term effects of tDCS should be clarified, and its optimal targets for motor and spatial rehabilitation have not been sufficiently studied yet. There is also a risk of misuse or overuse of non-invasive stimulations. Finally, local rehabilitation teams will be coordinated for inter-site standardization of inclusion, occupational therapy tasks, test performance and stimulation tools use.

In conclusion, the originality of our study lies in this novel combination of non-invasive stimulation techniques with low attentional demands and their application during occupational therapy sessions, thus ideally complementing conventional rehabilitation. The results of our multimodal approach should also provide interesting data to reconsider hemi-spatial theories suggesting a dominant function of the right hemisphere or others supporting an “interhemispheric competition” model [49].

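### Three centres with unmodified local rehabilitation, but no stratification by centre is stated and the stated analyses ignore centre, so centre differences in recovery stay in the error term and can shift an arm contrast by chance

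*Protocol article*

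**What the plan says.** **Setting.** Section 2 of the protocol article says the trial "will take place in three neurological rehabilitation centers in Grand-Est and Provence-Alpes Côte d’Azur regions, France". Section 2.4.1 has the experimental treatments "administered by trained occupational therapists". Section 2.4.2 leaves all other rehabilitation as it is: physiotherapy, speech therapy, the occupational therapy sessions on the other two days, and the second part of each experimental session.

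**Allocation.** Section 2.4.1 gives "centralized randomization in a 1:1 ratio performed using a custom made algorithm on Matlab" for four groups. No stratification factor is named. Section 2.5 states: "we estimated that 48 patients would be necessary for our study, randomly and homogeneously distributed in each of the 4 groups". That sentence concerns group totals.

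**Analysis.** Section 2.6 names test period as the within-subject factor and "treatment groups (control, left-NMV, left-NMV + sham-tDCS, left-NMV + a-tDCS) as between-subject factors". If assumptions fail, it compares groups by Kruskal–Wallis tests on Post–Pre differences, with no centre stratum. The comparability check in 2.5 covers sex, age, education, illness duration, baseline CBS and stroke location, but not centre.

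**Control of centre differences.** The Discussion says "local rehabilitation teams will be coordinated for inter-site standardization of inclusion, occupational therapy tasks, test performance and stimulation tools use". Section 2.4.4 adds monitoring of 10% of experimental sessions and 10% of evaluations, and evaluators blind to group.

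**The concern.** Most of what each patient receives over the study is the centre's own rehabilitation, and the primary outcome is the evolution of a functional scale. Centres may plausibly differ in how much their patients improve. If so, two things follow from the analysis as stated.

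- Between-centre variation in recovery sits in the residual and costs precision.
- If one arm happens to draw more of its patients from a centre with faster recovery, that arm's change is shifted, and no stated analysis removes the shift.

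The trial has little precision to spare. Section 2.5 says "No a priori power calculation could therefore be performed". With 12 patients per arm, a pairwise comparison reaches 80% power only at a standardised difference of about (1.96 + 0.84) × √(2/12) = 1.14.

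**Working it through.** **Inputs from the article.** N = 48, 4 groups, so 48/4 = 12 per arm; 3 centres; α = 0.05. No effect size, SD or power is given, so 48 cannot be re-derived by a power formula.

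**Assumptions, because the article gives no figures.** 16 patients per centre; centre accounts for a share f of the variance in CBS change, with f = 0.05, 0.10 or 0.20; centre effects of −s, 0 and +s, so s = √(1.5f) in SD units of change; one arm shifted by 1.2 SD for the power figures.

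**1. Chance imbalance.** 48 patients were allocated at random to four arms of 12, ignoring centre (20,000 or more draws):

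| Event | Unstratified, 12 per arm | Stratified by centre |
|---|---|---|
| Some centre-by-arm cell has 0 or 1 patient | 32% | 0% |
| Some centre-by-arm cell is empty | 4% | 0% |
| a-tDCS and sham arms differ by 4 or more in a centre | 29% | 0% |

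**2. Shift of an arm contrast.** Under unstratified allocation, the random shift between two arms has SD √(f × (48/47) × (1/12 + 1/12)). This gives 0.09, 0.13 and 0.18 SD at f = 0.05, 0.10 and 0.20. The sampling SE of the contrast is √(2/12) = 0.41 SD. For a poor draw, with one arm split 6/4/2 over the centres and the other 2/4/6, the shift is s × 8/12:

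- f = 0.05: 0.274 × 8/12 = 0.18 SD
- f = 0.10: 0.387 × 8/12 = 0.26 SD
- f = 0.20: 0.548 × 8/12 = 0.37 SD

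**3. Type I error and power.** One-way F test on change, 3,000 simulated trials per cell (simulation SE about 0.004 for type I error and 0.007 for power near 0.84):

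| f | Power: unstratified, no centre term | Power: unstratified, centre term | Power: stratified, centre term | Type I: unstratified, no centre term | Type I: stratified, no centre term |
|---|---|---|---|---|---|
| 0 | 0.841 | 0.827 | 0.836 | 0.050 | 0.050 |
| 0.05 | 0.839 | 0.839 | 0.865 | 0.052 | 0.041 |
| 0.10 | 0.840 | 0.869 | 0.880 | 0.047 | 0.033 |
| 0.20 | 0.844 | 0.902 | 0.914 | 0.052 | 0.024 |

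As a check on the stratified, adjusted column, the noncentral F with 3 and 42 degrees of freedom and noncentrality 12 × 1.2² × 0.75/(1 − f) gives 0.854, 0.874 and 0.912. With 44 degrees of freedom and f = 0 it gives 0.835. The gain at a 5% share is therefore about 2 points at most.

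Stratifying without a centre term brings no gain in power (0.841 to 0.844 at these shares) and makes the test conservative.

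**4. Which term does the work.** In the mixed ANOVA the evolution of CBS is tested by group-by-period, in the within-subject part of the model. A centre main effect enters only the between-subject part, so it leaves that test unchanged. Centre-by-period is needed there, or else centre as a term in a model of change.

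**The case against.** Four objections carry weight.

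**Silence is not a plain draw.** A reader might infer that the allocation is an unrestricted draw. The article does not say so: it names a custom algorithm, and Section 2.5 implies equal arm totals. Stratification may be described in the full protocol, which is not shown. All that can be said is that none is stated. The analysis is different: factors, periods, groups and fallback are all spelled out, and centre is in none of them.

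**Stable offsets cancel.** A reader might infer that a lenient rater or a milder case-mix at one centre would bias the result. A difference that is constant over time drops out of group-by-period and of Post–Pre differences. Only centre differences in recovery matter.

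**No inflated false-positive rate.** A reader might take the larger error to mean type I error. Averaged over unstratified allocations it stays at 0.047 to 0.052. Even under the poor 6/4/2 versus 2/4/6 split it is only 0.055, 0.056 and 0.062 at the three shares. What grows is the residual variance, by 1/(1 − f): 1.05, 1.11 and 1.25 times.

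**The size is assumed and small.** Centre sizes and centre shares appear nowhere in the article. With centres at −0.5, 0 and +0.5 SD, the chance shift has SD √((8/47)/6) = 0.17. Added in quadrature to 0.41 this gives 0.44, about 8% more. Standardisation, monitoring and blinded evaluation may reduce centre differences further, although they cannot undo an imbalance once it has arisen.

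**Conclusion.** The point holds as a modest matter of precision and robustness, not as a threat to validity. The stated ANOVA and its fallback ignore centre in a three-centre trial with unmodified local therapy, and no stratification by centre is stated. The benefit of accounting for centre runs from near zero (or a loss of about a point if centre does not matter) through at most about 2 points at a 5% share to roughly 3 to 7 power points at 10 to 20%. This rests on equal centres of 16, 12 per arm, a 1.2 SD shift in one arm, and a one-way test on change as a stand-in for the five-period ANOVA. Unequal centres would change the imbalance figures. The omission from Section 2.6 stands whether or not the full protocol stratifies; if it does, leaving centre out makes the test conservative.

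**What to change.** **Section 2.4.1.** State the ratio as 1:1:1:1, and state that the central sequence is stratified by centre, with randomly varying block sizes that are concealed from the sites. If the full protocol already stratifies, say so here.

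**Section 2.6.** Include centre and centre-by-period in the mixed ANOVA, or fit a model of CBS change with centre as a term. In the fallback, replace the Kruskal–Wallis test on Post–Pre differences with a centre-stratified rank test.

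**Cost.** A change to the allocation program and a few degrees of freedom: 2 for centre, plus (3 − 1) × (5 − 1) = 8 in the within-subject part for centre-by-period. Blocks left incomplete at the end of recruitment may leave the arms slightly unequal. Because the control, vibration-only and tDCS arms look different to the therapists, blocking within centre makes some allocations predictable; varying and concealing the block sizes reduces this but does not remove it. The analysis terms can be fixed before any data are analysed, even if recruitment has begun.

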#### 2.4.2. Setting of Interventions

During the first 15 min of the occupational therapy sessions, without modifying the classically performed exercises, the therapist will be invited to solicit voluntary upper limb movements in patients’ peri-personal space, without looking for performance or speed, but rather for a qualitative execution. The patients’ position will be verified to ensure that they are sitting in front of the table. In the initial experimental phase (during the first sessions), in order to maintain a maximum level of motivation, patients will have the option of mobilizing their ipsilesional upper limb instead of the contralesional one to perform these different exercises. The use of the latter will be gradually increased, avoiding as much as possible the patients performing bimanual activities in their neglected hemi-space [36,37].

No modification of the conventional rehabilitation will occur such as daily physiotherapy, speech therapy, adapted physical activities, Tuesday and Thursday occupational therapy sessions, and the second part of experimental occupational therapy sessions.

#### 2.4.3. Setting of Assessments

In this study, the primary outcome will be the evolution of the global USN behavior evaluated by the Catherine Bergego Scale (CBS) [38], a functional scale assessing USN severity in daily life situations.

In addition, various USN spatial cognitive-motor skills will be assessed as secondary outcomes by the following five tests.

The Fluff test [39] aims at investigating personal neglect with targets attached to patients’ clothes, as illustrated in Figure 2a. The number of removed targets will be counted in order to calculate a score of personal neglect expressed as the difference of percentages of targets found on each side of the body (left–right), this value becoming more negative with the severity of personal neglect.

Gainotti’s drawing copying test [40], illustrated in Figure 2b, informs us on two kinds of peri-personal neglect referring to distinct disturbances of mental representations involved: space-centered neglect (egocentric) and object-centered neglect (allocentric). Therapists will verify throughout the test that the patient remains centered in relation to the paper. The quality of the drawing will be evaluated with respect to allocentric and egocentric reference frames.

The Map of France test [41] is designed to investigate representational neglect. The number of cities mentioned by the patient will be counted on either side of a median line drawn vertically through the center of France (Lille–Perpignan axis; see Figure 2c). A mental evocation score will be calculated as the ratio of the number of cities on each side of this axis (left/right). In addition, the strategy and order of mention will be recorded for qualitative analysis.

The Subjective Straight-Ahead test (SSA) [21] investigates the accuracy of egocentric perception, using the experimental device pictured in Figure 2d. The centered position of the patient will be verified throughout the test. Egocentric perception will be expressed as the mean error of 20 successive trials, after measuring for each trial the angular difference between the measured angles of the hand pointed toward the SSA direction and the objective straight-ahead direction of the patient’s body. A higher score indicates a less accurate egocentric perception; leftward errors will be assigned as negative values and rightward errors as positive values.

The Wheelchair navigation test [21], illustrated in Figure 3, aims at investigating spatial navigation skills and extra-personal neglect. The ride will be carried out once in each direction (A-B and B-A) to balance the number of obstacles and turns to the left and right. The time taken to finish the course will be measured and the number of bumps counted. Navigation quality will also be observed qualitatively (obstacle avoidance, goal strategy, perseverations).

Each test will be carried out several times over the study by a trained occupational therapist:

Baseline assessment (Pre): During the first week, each test (except for the CBS realized only once) will be repeated three times in order to obtain a reliable estimation of the participants’ performance level (mean values) before starting the experimental interventions.

Follow-up assessments: These will take place just at the end of the first experimental session (Postsession1), after the first and third weeks of the protocol (Postweek1 and Postweek3, respectively) and there will be a final evaluation three weeks after its ending (Postweek6). In addition, all patients will be asked about their expectations and satisfaction regarding the treatment at the end of each week of intervention.

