It is well established that USN is an independent factor associated with poor prognosis and functional outcome after stroke [6], and consequently, the rehabilitation of this syndrome is a challenging issue. Conventional rehabilitation of USN is mostly based on visual scanning training, the first developed method, which aims at better visual exploration toward the contralesional side [7]. The effectiveness of this “top–down” approach is based on the stimulation of attentional resources and requires patients to be aware of their impairment in order to actively correct it. However, since attentional capacities are often altered after stroke and especially in patients affected by USN [8], other rehabilitation methods, called “bottom–up” approaches, favor sensory manipulations either by deceiving the patient’s body perception (vestibular stimulation, optokinetic stimulation, neck muscle vibration), which is costless in terms of attentional resources, or through cognitive adaptation induced by visuo-haptic distortion (visual prisms) [9]. Both showed interesting results in early-phase rehabilitation [10,11]. Among these “bottom–up” techniques, neck muscle vibration (NMV) consists in applying a 80–100 Hz vibration on the skin over the upper fibers of one of the trapezius muscles, creating a proprioceptive illusion such that the body midline and surrounding space are perceived to be shifted to the stimulated side [12]. Some studies have shown a persistent reduction in USN symptoms thanks to left-side NVM [13,14]. For instance, Kamada et al. [15] showed that applying this illusory technique for 5 min right before an occupational therapy session optimized its beneficial effects as quantified by the conventional Behavioral Inattention Test (c-BIT) [16], a neglect-specific test battery, and the Functional Independence Measure (FIM) [17]. In addition, several studies suggest that combining different therapeutic approaches with converging effects may lead to the best benefits on USN [18,19]. Left-side NMV appears to be ideal for combination with other rehabilitation techniques, given its safety, simplicity of use, passive nature and particular therapeutic effects. USN reduction was shown to persist when NMV was coupled with visual scanning training [20] or applied in a visuo-haptic feedback context [21]. This feedback context was achieved through repeated reaching movements similar to the motor activities usually performed during patients’ conventional rehabilitation sessions. These results therefore support the interest of associating the left-side NMV technique simultaneously to rehabilitation sessions for left USN patients.

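### The signed Subjective Straight-Ahead score is read as accuracy with higher meaning worse, which fails for any leftward mean; as a minor point, the Map of France ratio is unbounded and can be undefined

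*Protocol article*

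**What the plan says.** **SSA.** Section 2.4.3 of the protocol article says that the test "investigates the accuracy of egocentric perception". The score is defined there: "Egocentric perception will be expressed as the mean error of 20 successive trials". The reading rule and the sign convention follow in one sentence: "A higher score indicates a less accurate egocentric perception; leftward errors will be assigned as negative values and rightward errors as positive values". No absolute value is taken at any step. The Introduction describes the effect of neck-muscle vibration (NMV) as one in which "the body midline and surrounding space are perceived to be shifted to the stimulated side"; in this trial the stimulated side is the left.

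**Map of France.** The same section states: "A mental evocation score will be calculated as the ratio of the number of cities on each side of this axis (left/right"). For the Fluff test it uses a difference instead, "expressed as the difference of percentages of targets found on each side of the body (left–right").

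**Analysis.** Section 2.6 lists the variables entered as quantitative data, among them "CBS scores, those of personal neglect, mean egocentric errors and mental evocation". They go into a mixed ANOVA. If its assumptions fail, they go into rank tests, with the groups compared on follow-up minus mean baseline. A participant with a missing score at any session is left out of the analysis of that test.

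**The concern.** On a scale where left is negative and right is positive, the best value is 0 and performance worsens in both directions. A rule that higher is less accurate treats the scale as if it worsened in one direction only. A patient who points well to the left of straight ahead then gets a better score than a patient who points straight ahead.

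This bears on the treatment comparison because three of the four groups receive left NMV and the control group does not. If vibration carries some patients past the midline, the misreading would fall on the treated groups and would favour them.

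The Map of France ratio raises a separate and smaller point. Its denominator is a count that may be small or zero, so the formula itself can produce extreme or undefined values.

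**Working it through.** The article gives no numerical result for either score, so there is no figure to reproduce. The values below are illustrations or stated assumptions.

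**SSA, order.** Let m be the signed mean of the 20 trials (2.4.3). The size of the deviation is |m|. The rule needs the score to rise with inaccuracy, but m and |m| rise together only when m ≥ 0. At m = −8 the score lies below 0, so the rule reads it as better than perfect, while |m| = 8.

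**SSA, change.** Section 2.6 uses follow-up minus baseline in the rank-based route; the ANOVA compares the same signed values over time.

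| Baseline | Follow-up | Signed change | Change in size of deviation |
|---|---|---|---|
| +6 | 0 | 0 − 6 = −6 | 0 − 6 = −6 |
| +6 | −6 | −6 − 6 = −12 | 6 − 6 = 0 |

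The second patient shows 12/6 = 2 times the signed change of the first, with no reduction in the deviation.

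**SSA, group mean.** If half of a group is at +6 and half at −6, the signed group mean is (6 − 6)/2 = 0, yet every patient is off by 6.

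**SSA, unsigned alternatives.** Simulation of 20 normal trial errors, with bias and trial SD assumed, gives these mean absolute errors:
- bias −8 or +8, SD 3: 8.0 in both cases
- bias 0, SD 3: 2.4
- bias 0, SD 10: 8.0

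The mean absolute error does obey the rule that higher is less accurate, but it also contains trial scatter. The absolute value of the mean is much less affected by scatter. With no bias and normal errors its expected value is 0.798 × SD/√20, which is 0.54 for SD 3 and 1.78 for SD 10.

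**Map of France, shape.** Mirror-image results of 1 left, 3 right and 3 left, 1 right score 0.33 and 3. The index (L − R)/(L + R) gives −0.5 and +0.5.

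**Map of France, undefined values.** City counts are not given. Assume independent Poisson counts and 7 administrations (3 at baseline and 4 at follow-up, 2.4.3). Then p = P(R = 0) = exp(−mean R), and the chance that a patient has at least one undefined ratio is 1 − (1 − p)^7.

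| Assumed mean right count | p | At least once in 7 |
|---|---|---|
| 2 | 13.5% | 64% |
| 3 | 5.0% | 30% |
| 4 | 1.8% | 12% |
| 6 | 0.25% | 1.7% |
| 12 | below 0.01% | about 0% |

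With assumed means of 2 left and 4 right, the index is undefined only if no city at all is named: p = exp(−6) = 0.25%, or 1.7% over 7 administrations, against 12% for the ratio. The simulated mean of the ratio in that case is 0.66 against 2/4 = 0.50; the mean of the index is −0.333 against (2 − 4)/(2 + 4) = −0.333.

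**The case against.** **SSA.** The best defence is that all patients have left neglect, and the Discussion presents left NMV as offsetting their egocentric deviation. A signed mean measures exactly that deviation, and among rightward errors higher is indeed worse. On this view the sentence is loosely worded: higher may mean larger in size, with the next clause giving only the direction. This stands in part. The signed mean is a legitimate measure of bias, and the raw data allow either reading. But the text does not say that size is meant, and section 2.6 carries the signed value into the analysis.

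A reader might infer two stronger things:
- *That averaging signed trials is itself a mistake because left and right errors cancel.* It is not. That is how a bias is estimated from repeated trials, and the mean absolute error has the opposite weakness: 8.0 results from a bias of 8 with SD 3 and equally from no bias with SD 10.
- *That the trial will report overshoot as its largest gain.* The article contains no SSA data and nowhere calls a negative value an improvement. The Introduction describes an illusion caused by applying vibration, whereas assessments come after a session or weeks later. A negative group mean would also be visible to the analyst.

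**Map of France.** In left neglect the right side is normally the spared side, so a zero denominator should be uncommon. For one administration the ratio r and the index (r − 1)/(r + 1) rank patients identically, and section 2.6 moves to rank tests if normality fails. That helps only partly, since averaged baselines and change scores do not keep the same ranks under the two formulas. A rule for zero counts may stand in a fuller document that is not shown. A reader might infer that a large share of patients would drop out of this test. The article does not support that: the rates depend wholly on assumed counts, and it does not say that an undefined ratio is treated as missing.

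**Conclusion.** The SSA point holds as an error in the stated scoring rule: for any leftward mean the rule gives the wrong reading. The contradiction needs no assumption. Its practical size does: it depends on how many patients have a leftward mean error, which the article makes plausible through the expected effect of left NMV but does not show. In the worked case the signed change is twice that of full correction, with no gain in accuracy.

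The Map of France point is minor and optional. The ratio is unbounded, asymmetric and undefined at a right count of zero. Under the assumed Poisson means this affects from about 0% of patients (12 right-side cities on average) to 12% (4 cities), and more only if fewer are named.

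Both scores are secondary. The Catherine Bergego Scale outcome and the sample size are untouched.

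**What to change.** **SSA (should be changed).**
- In 2.4.3, state that the signed mean is directional bias, left negative and right positive, with best value 0. Delete the first clause of the quoted sentence for that score.
- Name an unsigned score as the accuracy measure in 2.6: either the absolute value of the mean error, or the mean absolute error with a note that it also contains trial scatter.
- Compute it at each administration before averaging the three baseline values, so that baseline and follow-up are built alike.
- Report the signed mean alongside, which keeps comparability with earlier signed results.

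**Map of France (optional).** Replace the ratio by (left − right)/(left + right), which runs from −1 to +1 and is similar to the difference already used for the Fluff test. State what is done when no city is named. The index does not remove the floor: with no left-side city it is −1 whatever the right count, just as the ratio is 0.

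The cost is a few lines of scoring text. The raw data, assessments and design stay the same. The choice should be fixed before results by group are seen.
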